**Figure 1 F1:**
[figure not shown]
Flow chart of the SleepTrackTXT pilot trial.

### Setting

We will begin recruitment using email lists of emergency physicians, emergency nurses, and other emergency technicians working or training at one of three emergency departments (EDs) affiliated with a large academic medical center, the University of Pittsburgh Medical Center in Pittsburgh, Pennsylvania. The recruitment webpage is visible by any emergency worker in the United States. For those outside the academic health system, we anticipate a diverse sample from across the United States will be exposed to study recruitment via our study webpage. The total number of emergency workers expected to have an interest in participating in the study is unknown.

### Recruitment protocol

After an emergency worker views the website an appointment for telephone screening and enrollment is made via email by the emergency worker. If eligible, subjects complete the following steps: 1) text the words ‘Sleep Track TXT’ to the study telephone number to register his or her cell or smartphone with the SMS system; 2) visit the study portal webpage and watch the informed consent video and make a selection to voluntarily participate or not (this is at time of enrollment); 3) if the subject agrees to participate, he/she will create a unique login and password; 3) the subject will then login and answer baseline survey questions that capture demographics and patterns of sleep, fatigue, and shiftwork; 4) the subject will then use a calendar tool to register his or her shift schedule for the next 90 days. Subjects can use the calendar tool to add or edit shifts at any time during the study. Consenting subjects will answer baseline survey questions and provide the contact information of at least one contact if needed for follow-up. This study has been approved by the University of Pittsburgh Institutional Review Board (IRB number: PRO13120428).

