**Methods/Design:**

We will conduct a pilot randomized trial with a convenience sample of adult EMS workers recruited from across the United States using a single study website. Participants will be allocated to one of two possible arms for a 90-day study period. The intervention arm will involve text message assessments of sleepiness, fatigue, and difficulty with concentration at the beginning, during, and end of scheduled shifts. Intervention subjects reporting high levels of sleepiness or fatigue will receive one of four randomly selected intervention messages promoting behavior change during shiftwork. Control subjects will receive assessment only text messages. We aim to determine the performance characteristics of a text messaging tool for the delivery of a sleep and fatigue intervention. We seek to determine if a text messaging program with tailored intervention messages is effective at reducing perceived sleepiness and/or fatigue among emergency medicine clinician shift workers. Additional aims include testing whether a theory-based behavioral intervention, delivered by text message, changes ‘alertness behaviors’.

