### Remuneration

All participants will receive the following incentives: a coffee mug and $10 gift card at completion of enrollment, a $10 gift card at completion of 30 days, and again at completion of 60 and 90 days, and entry into a drawing for one of five tablet computers for completion of all components of the study. We believe this plan will incentivize adherence without creating unrealistic expectations for compliance in further studies.

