#### Shift level measures and primary outcome

Our performance outcome of interest is subject compliance with text message assessments. Our primary intervention outcome of interest is self-reported fatigue at the end of scheduled shifts. Single-item measurement is the preferred approach for research that involves real-time data capture and/or ecological momentary assessment (EMA) [39,40]. We based the construction of our single-item outcome measure and the scale for respondents to record their subjective response on prior EMA research of insomnia [41]. We hypothesize that study subjects in the intervention group will report lower levels of fatigue at the end of shift than study subjects in the control group.

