#### Sample size

In planning the study, several unknowns prevented a well-informed sample size analysis including the number of shifts each participant would contribute and the amount of correlation in fatigue between multiple shifts within the same subject. We assumed that compliance would be high for all study subjects, with over 80% of text message assessments answered [42]. Due to the pilot nature of the study, we conservatively assumed a minimum of one observation per person and then determined the number we would need to see a large effect size for the ‘proof-of-concept’ outcome. Based on our previous cross-sectional data [15,16] we assumed that 50% of EMS workers would report fatigue at the beginning of or during shift (at risk population). If N = 25 per study arm, we will have 80% power to detect a large effect size of 0.78 difference in the mean end of shift fatigue score between control and intervention groups (alpha = 0.05), using a two-sample Mann-Whitney U test power analysis (PASS software, NCSS Statistical Software, Kaysville, Utah, United States) assuming the actual distribution is logistic. Given the 50% expected rate of fatigue at baseline, we will recruit and randomize 100 participants (50 per group) to obtain the ‘at risk’ number needed within each arm.

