#### Statistical analysis

We will describe overall number of shifts per provider and the mobile text participation for all study subjects. For example, we will quantify compliance with our text message queries and the number that were lost to attrition. We will use linear mixed-model analyses to examine the effectiveness of the intervention on reducing reported fatigue at the end of shift among all participants and among only those reporting fatigue at baseline. We will construct a model where the outcome is the reported fatigue at the end of each shift, a fixed effect for experimental group, a fixed effect of time in study, and a random effect for subjects to account for multiple shifts within each person. We will examine the estimated change in fatigue score per shift in the intervention group compared to the control group. Post-estimation testing will be used to describe the correlation in fatigue scores within the subjects across shifts. The same methodology will be used to analyze end of shift sleepiness and difficulty in concentrating.

The eight scale components of the SFAB survey are measured at baseline and at the end of the study. Likert responses will be scored as continuous measures and weighted from 0 to 100, with higher scores indicating more positive scores. We will test for changes over time and between-group differences in these scales using one sample and two sample t-tests, assuming the underlying distribution of the outcomes are normal. If the data are highly skewed we will use non-parametric tests including the sign rank test and Mann-Whitney U test. All statistical testing will be two-sided with alpha set at <0.05 using STATA version 10 SE (StataCorp LLP, College Station, Texas, United States) and SAS version 9.2 (SAS Institute Inc., Cary, North Carolina, United States).

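### Compliance is measured on texts generated by a calendar that subjects enter and can edit, so removed or never-added shifts leave the denominator and can only raise the reported rate

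*Protocol article*

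**What the plan says.** The section on shift level measures states: "Our performance outcome of interest is subject compliance with text message assessments". The Sample size section gives the planning value: "We assumed that compliance would be high for all study subjects, with over 80% of text message assessments answered". The Statistical analysis section says "we will quantify compliance with our text message queries and the number that were lost to attrition", and just before that: "We will describe overall number of shifts per provider and the mobile text participation for all study subjects".

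The texts follow the shift schedule. The abstract describes "text message assessments of sleepiness, fatigue, and difficulty with concentration at the beginning, during, and end of scheduled shifts", and Table 1 places assessments at the start of each scheduled shift, every 4 hours during it, and at its end. The schedule comes from the subject. Under Recruitment protocol, "the subject will then use a calendar tool to register his or her shift schedule for the next 90 days", and then: "Subjects can use the calendar tool to add or edit shifts at any time during the study". The article mentions no check against an employer roster and no frozen copy of the enrolment calendar.

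**The concern.** The person whose compliance is being measured also controls how many texts fall due. A subject who tires of the texts can ignore them, which lowers the rate, or can remove future shifts or stop adding them, which leaves the rate untouched. The two kinds of disengagement mean the same for the tool's usefulness, but only the first shows in the compliance figure.

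The Discussion gives reasons to expect some fatigue with the texts. It names compliance with the 4-hourly assessments as the main methodological challenge, expects that texts may seem repetitive, and notes that long shifts bring many more of them.

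What is at stake is the first objective, the performance of the text tool over 90 days. The authors hypothesise high compliance and say in the Discussion that evidence of compliance could support wide expansion. A rate that is biased in the favourable direction by an unknown amount is weak support for that step.

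**Working it through.** **The plan's own figures.** The article gives no compliance figure to reproduce, only the planning assumption of over 80%. The sample size calculation assumes one observation per person and does not depend on this point. Its stated 80% power (25 per arm, effect size 0.78, logistic distribution) reproduces: 80.9% by an efficiency-adjusted noncentral t, 79.1% by simulation of the Mann-Whitney test.

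**Direction.** Let A be texts answered, S texts sent, and D texts that would have been due on worked shifts that were removed or never added.
- Compliance on texts sent = A / S.
- Compliance over all worked shifts = A / (S + D).

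Since D is zero or more, the first is never below the second. This is why the mechanism works in one direction only. A shift that was truly cancelled is not part of D, and its removal is correct.

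**Size.** Assumptions, none of them from the article except where stated:
- c = 0.85, the share of texts answered while a subject is active.
- f = the share of subjects who lapse.
- g = the fraction of the 90 days before the lapse (day 45 gives g = 0.5).
- r = the share of lapsed subjects who clear their calendar; the others leave shifts registered and unanswered.
- Equal shift rates for all subjects.

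Formulas:
- Over all worked shifts: c × [1 − f(1 − g)].
- Reported, on texts sent: c × [1 − f(1 − g)] / [1 − r f(1 − g)].

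With r = 1 the reported rate is c = 85.0% whatever f is. For a lapse at day 45:

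| f | All worked shifts | Inflation |
|---|---|---|
| 3.2% | 0.85 × (1 − 0.032 × 0.5) = 83.6% | 1.4 points |
| 5% | 0.85 × (1 − 0.05 × 0.5) = 82.9% | 2.1 points |
| 15% | 0.85 × (1 − 0.15 × 0.5) = 78.6% | 6.4 points |
| 30% | 0.85 × (1 − 0.30 × 0.5) = 72.3% | 12.8 points |

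The 3.2% is the upper of the attrition rates that the Discussion cites from other text-message studies (2.4% to 3.2%). It is an attrition or withdrawal rate and not a rate of calendar thinning, so it is only a reference point. Even with a lapse at day 0 it gives at most 0.85 × 0.032 = 2.7 points.

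**Sensitivity to how subjects lapse**, with f = 30% at day 45:
- r = 1: reported 85.0% against 72.3%.
- r = 0.5: reported 0.7225 / (1 − 0.5 × 0.30 × 0.5) = 0.7225 / 0.925 = 78.1% against 72.3%.
- r = 0: reported 72.3% against 72.3%, so no inflation.

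The bias therefore comes only from subjects who remove shifts or do not add them.

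**The case against.** The strongest reply is that the design already catches the commonest form of disengagement. Shifts for 90 days are registered at enrolment, so a subject who simply ignores the texts stays in the denominator. Inflation needs an active removal, or a failure to add later shifts. The text speaks of adding and editing; that editing includes deleting is a natural reading but is not spelled out. The plan will also describe shifts per provider, where an emptied calendar might show as a low count. All of this stands and limits the likely size. It does not remove the bias: a shift count may expose thinning, but it does not correct the rate, and it cannot by itself tell thinning from part-time work.

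A reader might infer more than the article supports:

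- **That the trial can declare success wrongly at 80%.** The figure is a planning assumption in the sample size section. No pass mark is set, and the hypothesis is only that compliance will be high.
- **That the incentives reward thinning the calendar.** The Remuneration section offers gift cards at 30, 60 and 90 days and "entry into a drawing for one of five tablet computers for completion of all components of the study", but does not say what completion requires. Ignoring the texts may serve a subject just as well.
- **That thinning differs by arm.** The intervention arm receives more messages, so this is possible, but nothing in the article shows it.
- **That the fatigue comparison is damaged in a further way.** The mixed model uses observed end-of-shift scores. An unanswered shift and a removed shift both contribute no score, so the fitted estimate is the same.
- **That emptied calendars will escape the attrition count.** The article does not define attrition. That definition may stand in a fuller document, and its absence is not criticised here.

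**Conclusion.** The point holds as a one-directional bias of unknown size in the performance outcome. It follows from three stated features: texts go only to scheduled shifts, the subject enters and can edit the schedule, and compliance is described as the share of texts answered. It rests on reading that share as answered over sent, which is the natural reading of the Sample size and Statistical analysis sections.

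The illustrative inflation is about 1.4 points if 3.2% of subjects empty their calendar at day 45 and about 6.4 points if 15% do, with 85% answered while active. It is zero if lapsed subjects leave their shifts registered. None of these lapse rates can be confirmed from the article. The point concerns how compliance is reported and interpreted; it does not touch the sample size or show a bias in the treatment comparison.

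**What to change.** Keep the calendar editable, since real schedules change, and make the effect of edits visible:

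1. Keep, or extract where the system holds it, a time-stamped history of calendar entries, edits and deletions.
2. Report compliance on texts sent as the main figure, labelled as an upper figure.
3. Add a lower figure that also counts as unanswered the texts due on registered shifts later removed without replacement. Count a moved or swapped shift once.
4. Show registered shifts per subject per 30 days, by arm, against the shiftwork pattern reported at baseline. This is needed because the lower figure cannot capture shifts that were never added.
5. Report the number of subjects with no registered shift for a prespecified period, separately from withdrawals.
6. Interpret high compliance in the light of both figures, without treating 80% as a pass mark.

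The cost is a data extraction and a few descriptive tables. There are two downsides. Genuine cancellations make the lower figure pessimistic for removed shifts. And because enrolment had closed and follow-up was under way when the article was accepted, edits already overwritten cannot be recovered. If no history exists, items 4 and 5 can still be tabulated from the calendar as it stands, and the compliance rate should then be described as an upper figure only.

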### Participants

Inclusion criteria are: 1) 18 years of age and older, 2) working in the emergency care setting as an emergency physician, emergency nurse, emergency medical technician or paramedic, 3) currently working shifts as part of their employment in the emergency care setting, 4) have an SMS-enabled cellphone or smartphone, and 5) are willing to take part in a research study that requires the sending and receiving of multiple text messages at the start, during, and end of shiftwork.

### Randomization

Subject randomization is done using an adaptive algorithm, which will assign participants with a 1:1 allocation, restricting the imbalance to no more than four between the groups. The random number generator and algorithm is embedded in the structured query language (SQL) software program that supports the text message-based intervention. Randomization happens during their first attempt to log into a unique and password protected web-based account connected to the SQL program and complete the informed consent procedures.

### Intervention: text message assessments with recommendations

The intervention group text message recommendations to reduce of sleepiness or fatigue target the following behaviors: 1) naps and rest time [5-10], 2) consumption of caffeine [11], 3) physical exercise [12,13], and 4) use of talking and conversation with partners on duty as a form of mental exercise to stay alert. Our intervention seeks to impact one or more predictors of ‘alertness behavior’ during shiftwork. We operationalize the predictors of alertness behavior and potentially modifiable factors using the Integrated Model of Behavior Change [34]. The model combines components and variables thought to be influential in understanding and predicting behavior [34]. Other models include the Health Belief Model, Social Cognitive Theory, and Theory of Reasoned Action [34]. The key components and variables of these models include: 1) an individual’s attitude, 2) his or her perceived norms, and 3) his or her self-efficacy with respect to performing one or more behaviors. Our intervention consists of four motivating messages or strategies sent to a study subject if he or she reports a high level of sleepiness or fatigue at the start or during their scheduled shift. Upon reporting a high level of sleepiness or fatigue the study subject is sent the following opening text message linking sleepiness or fatigue to bad outcomes: *‘*No joke *-* Being very sleepy or fatigued on duty can increase your risk of injury’. This message is then followed by one of four randomly selected strategies for reducing feelings of sleepiness or fatigue and improving alertness during shiftwork: 1) If you can, take a short 20-30 minute nap on duty; 2) Try drinking a caffeinated beverage like coffee to stay awake; 3) Try doing some stretches or other exercise to stay alert; 4) Stay alert by talking to your partner when work is slow. We developed the intervention strategy messages based on prior research showing a positive impact on perceived sleepiness, fatigue, or alertness [5-13]. The SMS-enabled dialog and strategy messages were developed by study investigators and are hypothesized to have an impact on the behavioral determinants of an emergency worker’s intention to maintain alertness and vigilance during shiftwork. Figures 2 and 3 provide an illustration and flow chart of SMS messages for all subjects (Figure 2) and intervention content (Figure 3).

**Figure 2 F2:**
[figure not shown]
Flow chart of SMS messages for all study subjects.

**Figure 3 F3:**
[figure not shown]
Flow chart of SMS messages for the intervention group.

### Control: text messaging assessment only

Individuals in the control group will not receive any recommendations for improving alertness and reduction in intra-shift sleepiness or fatigue (Figure 2). Control subjects will receive text messages for assessment only at the beginning, during, and end of shifts.

### Remuneration

All participants will receive the following incentives: a coffee mug and $10 gift card at completion of enrollment, a $10 gift card at completion of 30 days, and again at completion of 60 and 90 days, and entry into a drawing for one of five tablet computers for completion of all components of the study. We believe this plan will incentivize adherence without creating unrealistic expectations for compliance in further studies.

### Measures

#### Participant level measures

After completion of the informed consent process we will collect demographic data on age, sex, alcohol consumption, smoking status, perceived general health, employment status, and eight other demographic factors. Other baseline measures will include sleep quality, fatigue, attitudes about shift scheduling, and perceptions of work-related fatigue and recovery (see Table 1). Sleep quality will be measured with the widely used and reliable Pittsburgh Sleep Quality Index (PSQI) [35]. A PSQI score of 6 or more on a 21-point scale indicates poor sleep quality [35]. Mental and physical fatigue at work will be measured using the Chalder Fatigue Questionnaire (CFQ) [36]. The CFQ is an 11-item scale of mental and physical fatigue that has been used in multiple emergency worker populations and shown by psychometric testing to be reliable and valid [15,16]. A CFQ score exceeding one of two scoring benchmarks can indicate severe mental and physical fatigue. Attitudes about shift scheduling will be measured with the Schedule Attitudes Survey (SAS) [37]. The SAS is a 21-item scale that measures a worker’s attitudes about his or her shift schedule. The tool’s intended use was for schedule modification and design by employers. The SAS has been used in diverse populations, including EMS workers, and is shown to have positive psychometric properties of reliability and construct validity [20]. Higher scores on the SAS are interpreted as representing greater dissatisfaction towards one’s current shift schedule.

**Table 1 T1:** Schedule of measurements for the study in SleepTrackTXT pilot trial

**Measure**	**At baseline enrollment**	**Beginning of every scheduled shift**	**Every 4 hrs during scheduled shifts**	**End of every scheduled shift**	**Subject reports an injury (at end of shift, or at any time)**	**At 90-days end of study**
Demographic survey	X					
Pittsburgh Sleep Quality Index (PSQI)	X					X
Chalder Fatigue Questionnaire (CFQ)	X					X
Schedule Attitudes Survey (SAS)	X					X
Occupational Fatigue, Exhaustion, Recovery Scale (OFER)	X					X
Sleep, Fatigue, Alertness Behavior Survey (SFAB)	X					X
Hours of sleep in past 24 hours		X				
Rate sleepiness now		X	X	X		
Rate fatigue now		X	X	X		
How difficult is it to concentrate now		X	X	X		
Estimate total number of patients you saw during your shift				X		
Were you injured during your shift?				X	X	
Describe the type of injury and body part affected*				X*	X*	
Rate sleepiness at time of injury*					X*	
Rate fatigue at time of injury*					X*	
How difficult was it to concentrate at time of injury*					X*	
**Intervention group only**^ **a** ^						
During your shift, did you take a nap, drink caffeine, stretch or exercise, or talk to your partner to stay alert?				X		
What strategy did you adopt?				X		
Did it help reduce your fatigue or sleepiness?				X		

*if subject reports an injury.

^a^These measures are administered to the intervention group when a subject reports a high level of sleepiness, fatigue, or difficulty concentrating at the beginning or during shift assessments.

Work-related fatigue and recovery will be measured with the Occupational Fatigue Exhaustion/Recovery Scale (OFER) [38]. The OFER is a reliable and valid 15-item scale that measures acute fatigue, chronic fatigue, and inter-shift recovery. Higher OFER scores ( ≥80) indicate higher fatigue and greater ability to recover between shifts. At baseline and at 90-days follow-up we will measure a participant’s behavior and intention to engage in behaviors that improve alertness with the Sleep, Fatigue, & Alertness Behavior Survey (SFAB). We developed the SFAB based on the Integrated Model of Behavioral Prediction [34]. The SFAB is comprised of 83 candidate items intended to measure eight factors and domains considered to be predictive of behavioral intent to improve alertness during shiftwork. These eight domains include: 1) attitudes about improving or maintaining alertness on duty; 2) perceived norms regarding what the person or others (peers) think or feel about being sleepy or fatigued while at work; 3) self-efficacy regarding improving or maintaining alertness while on duty; 4) knowledge of behaviors for improving or maintaining alertness on duty; 5) salience (perceived importance) of specific alertness behaviors; 6) habits linked to sleepiness, fatigue, and alertness; 7) environmental constraints to performing specific alertness promoting behaviors; and 8) intention to perform one or more behaviors. We will administer the SFAB at baseline and at 90-days follow-up to categorize individuals into one of four behavioral categories and assess the following changes in behavior: 1) intention to reduce fatigue and sleepiness on duty and reports consistent use of alertness-promoting behaviors; 2) intention to reduce fatigue and sleepiness on duty and reports inconsistent or no use of alertness-promoting behaviors; 3) no intention to reduce fatigue or sleepiness on duty and reports consistent use of alertness-promoting behaviors; and 4) no intention to reduce fatigue or sleepiness on duty and reports inconsistent or no use of alertness-promoting behavior.

